## Other Analyses:

*Other quantitative analyses*: Responses to questions on Appendix 20 B will be analyzed through simple descriptive statistics in terms of top barriers to and facilitators of VMMC uptake by age, intervention type, and study Location.

*Other Qualitative analyses:* Audio recordings will be transcribed and translated into English by study staff. The data analyst will then review to confirm accuracy and content validity based on the original audio-recordings. During the translation, we shall strive to keep the phrases and words as in the spoken language, to capture the context to the extent that is closer to the original language. The transcribed FGD and IDI narratives will be imported into the Atlas-ti software (version 5.0), for analysis. Transcripts will be read in their entirety before coding. Thematic content analysis of the data set will be performed with the discussion and interview guides being used to code each of the transcripts. Additionally in vivo codes will be identified during the coding. Participant experiences, views and recommendations shall be extracted from the text, condensed by abstraction of both overt and latent emphases as well as their unique experiences and expressions, and sorted out by relevant content areas. Conceptual categories related to communication or talking points on VMMC will be developed from the resulting themes.

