**Study Arm 3: Combined IPC and DSO interventions:** In selected Locations, IPC and DSO interventions (as described above) will be implemented concurrently. This will be done to determine the effect of both interventions delivered jointly compared to each delivered singly, and compared to no intervention.

Delivery Process of IPC+DSO Intervention: Activities and processes described under IPC and DSO will be replicated in these Locations/villages. The RAs will inform their participants about DSO sites and non-DSO sites in their neighborhoods, to allow people make a choice on where to go. Participants will be informed that services continue to be offered at all other facilities regardless of age. Copies of *Appendix 17: ‘All You Need to Know About VMMC’ booklet* will be left with each person/family reached in IPC+DSO sites, for ongoing reference and to share with others.

Participants aged 25-39 years in DSO and DSO+IPC Locations seeking services in non-DSO sites will be asked question 2 in Appendix 20 B (*What or who influenced your decision to come to this site while there are VMMC sites dedicated to men your age in this Location?*). The information will be useful in understanding reasons for preference for non-DSO sites yet DSO sites are available.

**Study Arm 4: Control/No Intervention:** One-quarter of participating Locations has been randomly assigned to the Control or No Intervention or ‘standard of care’ Arm. In these Locations, participants will only be reached with information on VMMC with reference to the ’*All You Need to Know About VMMC’* booklet (Appendix 17) at the time of enrollment.

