### Activities that cut across study arms:

1. Intervention Delivery
   1. In all the study Locations all participants aged 25-39 years coming for circumcision will be informed about the sub-study 4 (Role of sexual partners in time to resumption of sex post-circumcision) and given informational flyer (Appendix 31).
   2. We will continue to monitor recruitment activities in all arms to document other VMMC recruitment approaches that may be provided through other channels and which may bias the results.
   3. At all study sites, comprehensive VMMC services will be provided routinely per Ministry of Health guidelines, which includes: VMMC education and risk reduction counseling, HIV testing and counseling, condom education and distribution, STI screening and treatment, and the surgical procedure.
   4. At the end of the counseling session all participants aged 25-39 years accessing VMMC services at any of our study sites will be taken through written consent process and asked one question on what/who influenced their decision to come for VMMC (Appendix 20 A: Written Consent Form with 2 Questions for MC Participants Aged 25-39 Years). The question will help to identify which messages / cadre of RA / approaches are effective in influencing decision-making for VMMC for older men. In addition, men in DSO locations going for services in non-DSO sites will be asked question 2 from the same tool (Appendix 20 B). This will help us to understand why, despite availability of DSO sites, some older men still choose to go to non-DSO sites. Information from the two questions will not be linked to the respondents; instead, the questions and possible answers will be pre-printed on a piece of paper on which staff will simply check a participant’s response and drop in a box for collection by data staff. We will run descriptive statistics to determine top actual facilitators for circumcision.
2. Monitoring of Demand Creation Activities across Study Arms

We have designed a monitoring tool (Appendix 19: Monitoring Form for Demand Creation Strategies) to document information at different stages of the study; the form will capture:

1. Questions asked by participants during delivery of the intervention
2. Any additional information given beyond what is contained in Appendix 17: ‘*All You Need to Know About VMMC*’ booklet) in DSO and Control Arms.
3. Routine recruitment for the VMMC program in all study Arms to document if similar strategies were used during the study period.

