# PHASE 5: ESTABLISHING ENDLINE MC UPTAKE/ESTIMATING IMPACT OF INTERVENTIONS

At Endline, we will review our Participants Master Log (Appendix 14) to identify those who did not go for VMMC at the 45 VMMC clinics participating in the study. We will use the telephone numbers obtained during enrollment to contact the participants. Those who say that they got circumcised but are not in our Participant Master Log, we will make an appointment and visit them at home, or another convenient location, to administer consent (Appendix 2C), conduct Endline interview (**Appendix 2D: Phone and In-Person Interview with Uncircumcised Men at Endline**) and verify their circumcision status. Those who report not having gone for VMMC will be asked why they did not go, and their response recorded in Appendix 2D. If more than one reason is given, the participant will be asked to rank the top three reasons from most to least important. As enrolled participants go for VMMC services, we will be recording in the study’s Participants Master Log that they have been circumcised. However, only those who go for VMMC at study-designated clinics where we have stationed Research Assistants to monitor uptake will be recorded in the Participants Master Log. Recognizing that some participants could choose to go for circumcision in non-study clinics, we will need to capture those ones as well. To do this, we will not call any person apart from men who are listed in our Participants Master Log. We will review VMMC program theater registers in non-study clinics located within the 12 districts where the study is being conducted and compare the names with those indicated on the Participants Master Log as having not gone for VMMC. For those where the three names of VMMC clients in theater registers match the three names in the Participants Master Log, we will contact them using the phone numbers registered in the Participants Master Log and NOT in VMMC theater registers. When calling, the TASCO participants who could have been circumcised at non-study clinics will be asked if they were enrolled in the study. If they were, we will schedule a visit at home and obtain consent and if willing, conduct endline survey and verify MC status; if not, they will not be contacted further.

Inclusion/Exclusion Criteria

Inclusion:

- - 1. Was enrolled in the main study
    2. Resident of the study village
    3. Did not go for circumcision per TASCO Study database

Exclusion:

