## Data Analysis:

***Aim 1:*** ***Compare the rate of uptake of VMMC services by men aged 25-39 years exposed to Inter-Personal Communication, Designated Service Outlets, and IPC+DSO.***

The main outcome measure of this study is VMMC uptake. To assess the rate of uptake of VMMC services by uncircumcised men aged 25-39 years, we will compare the proportion of men who accept to be circumcised across the intervention arms. Specifically, the proportion of men accepting to be circumcised in each of the three arms will be compared to the proportion accepting circumcision in the no intervention group. P-values will be adjusted for multiple comparisons using the Bonferroni method. In order to take into account the clustered nature of the data, we shall also employ statistical methods suitable for analysis of cluster-randomized trials, namely the multi-level logistic regression model via the generalized estimating equations (GEE) approach with a random intercept. The random intercept term will represent the differences in true log-odds between the Locations. Odds ratio of VMMC uptake comparing intervention groups to the control group with the same underlying uptake rate will be estimated. This model will simultaneously assess individual-level and Location-level factors associated with uptake of VMMC as well as the effect of the interventions. Most importantly, it will enable the assessment of the intervention at the level at which randomization occurred: the Location level.

As outlined above under Phase 4, we shall conduct an endline survey in all households with men aged 25-39 years to establish the post-intervention MC uptake, and for those circumcised, collect information on when and where they were circumcised. These will be compared with similar data collected at baseline, using the methods described in the paragraph above. In addition, we shall extract from our database information on age of participants receiving services in each Location/Cluster. We will also have a sense of effectiveness of each recruitment strategy from surrendered referral coupons and from responses to question 1 in Appendix 20 B, asked to men who come for MC and through Appendix 2, the number of men reported and/or verified as circumcised at endline. This information, collected from multiple sources and through multiple approaches, will be compared across different arms of the study.

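### The barrier half of the Appendix 20B analysis names a form that, as described, asks only men attending for circumcision and has no barrier question; the source, possibly a mix-up with Appendix 2B, needs correcting

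*Protocol*

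**What the plan says.** Other Analyses (other quantitative analyses) gives one source, Appendix 20B, for two outputs: the answers "will be analyzed through simple descriptive statistics in terms of top barriers to and facilitators of VMMC uptake". The breakdown promised is "barriers to and facilitators of VMMC uptake by age, intervention type, and study Location".

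The form is described elsewhere as follows.

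- Activities that cut across study arms sets who is asked and when. At the end of counselling, "all participants aged 25-39 years accessing VMMC services at any of our study sites will be taken through written consent process". Each man is then "asked one question on what/who influenced their decision to come for VMMC". The same item states the purpose of the analysis as finding the leading facilitators; barriers are not mentioned.
- Phase 4, Study Arm 3, covers the second question: men aged 25-39 in DSO and IPC+DSO Locations "seeking services in non-DSO sites will be asked question 2 in Appendix 20 B". It asks what or who led the man to that site when sites for his age group exist in the Location.
- Data Analysis, Aim 1, refers to "responses to question 1 in Appendix 20 B, asked to men who come for MC".
- The Informed Consent item under Ethical Considerations and Table 7 describe the same respondents and the same two questions.

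Reasons for not being circumcised are recorded on other forms. In Phase 5, "Those who report not having gone for VMMC will be asked why they did not go"; the answer goes on Appendix 2D, and a man who gives several reasons ranks his top three. Table 7 describes Appendix 2B as recording the main reasons for going or not going.

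**The concern.** An analysis sentence that names its source will be followed. Followed literally, this one sends the analyst to a form completed only by men who have overcome whatever barriers they faced, and it asks that form for something neither question covers. The barrier table would then be empty, or question 2 would be pressed into service and reasons for bypassing a dedicated outlet would be reported as barriers to circumcision. The second outcome is the worse one, because the table would look complete while answering a different question and would have no respondents in the Control and IPC arms. A programme reading the trial would want to know why men in each arm did not go. The forms that hold that answer are not named in the sentence that promises it.

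**Working it through.** The protocol gives no figure for this analysis, so there is none to reproduce. The check sets what is promised against what the form is described as collecting.

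1. **Respondents.** Four places (Activities that cut across study arms; Data Analysis, Aim 1; Informed Consent; Table 7) agree that 20B goes to men attending for circumcision. An enrolled man who does not attend never receives it.

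2. **Question 1.** It asks what or who influenced the decision to come. This is a facilitator item, and it can be tabulated in all four arms.

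3. **Question 2.** It asks why the man came to this site when a dedicated one is available. This concerns the choice between sites by a man who has already chosen circumcision. It is asked only of men from DSO and IPC+DSO Locations who attend a non-DSO site. By Table 2 those arms hold 11 + 12 = 23 of the 45 Locations; Control and IPC hold 11 + 11 = 22. Its absence from those 22 is by design, since they have no dedicated outlet to bypass. It matters only if question 2 is misused as a barrier item.

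4. **Result by output.** Facilitators: available from question 1. Site choice: available from question 2 in two arms. Barriers to uptake: not available from either question in any arm.

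5. **Who holds the barrier information.** Under the planning assumptions in Sample Size Determination (1,233 men per arm, uptake of 30% in control and 40% in an intervention arm), the men not circumcised would number:
   - Control: 1,233 × (1 − 0.30) = 863
   - Each intervention arm: 1,233 × (1 − 0.40) = 740

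   These men are outside 20B but not outside the study. Phase 5 has participants not recorded as circumcised telephoned at endline, and those who did not go give reasons on Appendix 2D. The counts are therefore ceilings on the number who could answer 2D at planned uptake; fewer will be reached.

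6. **Possible cause.** Phase 3 (baseline) calls the baseline interview form Appendix 2B but gives it a title about two questions for clients at counselling. That is the title Table 7 gives to 20B. Elsewhere (Phase 4, IPC delivery, and Table 7) Appendix 2B is the enrollment questionnaire with verification of circumcision status, and its described content, reasons for going or not going, fits a barriers-and-facilitators analysis.

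**The case against.** The strongest reply is that this is a wrong label and not a wrong analysis. The protocol demonstrably confuses 2B with 20B, and if 2B is read into Other Analyses, both outputs can be produced in all four arms. This is plausible, and it changes the description of the defect, but not the need to act: the sentence names 20B, and whoever carries it into a detailed plan would carry the error too. The reading is also not certain, because 20B really is the source of the facilitator result in Activities that cut across study arms.

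Second, barriers are analysed elsewhere. Phase 4 plans theme-coded tallies from Appendix 44, with frequencies and proportions, and the formative discussions and interviews are analysed for barriers. Both are true. But Appendix 44 covers only the IPC and IPC+DSO Locations, and the formative work takes place outside the trial Locations. Neither gives the promised breakdown across the four arms.

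Third, tabulations of a secondary questionnaire may properly be left to a statistical analysis plan, which is not shown. That stands against any complaint that the 2D and 2B tables are unspecified. It does not answer the point that a source is named which cannot give its stated output.

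Fourth, the text of 20B is not available, so its content is inferred. The descriptions are consistent, however, and Phase 4 gives the wording of question 2 itself.

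**Conclusion.** The point holds for the barrier half of the sentence only. As described, Appendix 20B supports facilitators and site choice; it cannot supply barriers to uptake. The error is in the named source, possibly through a 2B/20B mix-up.

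Three stronger inferences are not supported. A reader might conclude that the whole analysis fails; it does not, because question 1 yields facilitators and the section describing the form already limits its analysis to them. A reader might conclude that the trial collects nothing from men who stay uncircumcised, so that 740 to 863 men per arm are lost; they are not, because those reached at endline give reasons on 2D. A reader might conclude that the trial's explanation of a small or null effect is compromised; the protocol assigns no such role to this table, and ranking barriers is not among its three aims.

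The size is therefore modest: one secondary descriptive output, with no bearing on the primary outcome, the power or the costing. It is still worth correcting, because the repair is nearly free and the literal reading could produce a mislabelled table. The conclusion rests on 20B containing what five places in the protocol say it contains.

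**What to change.** In Other Analyses, replace the sentence so that:

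- Appendix 20B is used for facilitators (question 1) and, in DSO and IPC+DSO Locations, for site choice (question 2) only.
- Barriers come from the ranked reasons on Appendix 2D among enrolled men reached at endline who did not go for circumcision. The Appendix 2B baseline reasons, among men uncircumcised at baseline, are shown alongside.
- Both barrier tables are given by arm, age and Location, with the number of men asked as the denominator. The 2D table should be labelled descriptive, since the men in it are selected by not having gone and by being reached.
- The Appendix 44 tallies are kept as a supplement for the IPC and IPC+DSO Locations only.

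In Phase 3, correct the title given to Appendix 2B.

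Two small checks belong with this edit. Table 7 lists 2B and not 2D among the endline forms, so it should be aligned with Phase 5. The 20B answers are collected on slips not linked to respondents, so the sponsor should confirm that each slip carries age group and Location; otherwise the facilitator breakdown cannot be made either.

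The cost is a wording change and a few extra tables. No new data are collected.

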## Data security

The following general security measures will be considered to ensure integrity of our data:

1. We will develop SOPs for data security and confidentiality procedures at collection, transfer, entry and storage levels, and make these readily accessible to all staff members who have access to confidential, individual-level data;
2. We will train staff on these procedures, including the use of passwords and codes to allow access to confidential information or data;
3. We will ensure all data are kept under lock and key, that access to confidential data is only limited to authorized persons, and that released data contains no identifiable information;
4. The study funder (PEPFAR and CDC) s well as the IRBs (KNH and CDC), will have unlimited access to data as long as they too comply with confidentiality conditions;
5. At the end of the study, data will be kept by IRDO for up to 10 years for electronic version and up to 5 years for paper forms, including consent forms. The PI (KA) will take responsibility of all study procedures, including long-term storage and disposition of data.

**Duration of Study:** The study will be in 45 Locations in 11 districts in former Nyanza province, and will take up to two years to complete.

**ETHICAL CONSIDERATIONS**

1. Ethical Review and Oversight: The proposal will be submitted to the Kenyatta National Hospital Ethics and Research Committee (KNH-ERC) and CDC Atlanta for ethical review and approval; KNH-ERC will also provide ongoing ethical oversight for the study; annual renewals will be obtained from both IRBs.
2. Potential risks and their Mitigation: Asking participants about their circumcision status and also verifying the same may be embarrassing to participants.

The RA will ask the participant to select a private location where MC status can be verified; we will do our best to keep study participants’ information private. However, there is a very small chance that someone outside of the research team may access information about the study – this is included in the consent document.

During sample collection for unlinked testing, we do not expect any new or unexpected adverse events outside of those normally occurring among persons receiving HTC and newly identified HIV-infected persons being enrolled in HIV care and treatment services.  These include negative reactions to an HIV diagnosis, incorrect test results, and breaches of confidentiality. There could also be a possibility of prolonged bleeding. If confidentiality is breached, this will be reported to the study coordinator within 24 hours of awareness and the coordinator who will report to the PI. The PI will send a written report to KNH-ERC via courier and to CDC IRB as email attachment within 24 hours of notification. Other protocol deviations (PDs) will be monitored by study staff and reported to the coordinator within 24 hours of receiving information;. All minor incidents that do not change the risk/benefit profile of participants (e.g. incorrect enumeration, listing of ineligible participants [not minors], etc.) – shall be reported with the annual IRB renewal. However, for more serious incidents and protocol violations that alter the risk/benefit profile of participants (e.g. enumerating in non-randomized villages, conducting interviews with ineligible participants), we shall continue to report any of those incidents immediately. The PIs will report urgent PDs within 48 hours and non-urgent ones annually, together with application for annual renewal. We have developed a tool (Appendix 28) for reporting incidents and protocol deviations.

The 2 questions in Appendix 20B will be asked, and IDIs (Appendices 9, 10, 12 & 13) conducted individually and in private. All respondents will be assured of confidentiality, that their names would not be written on the questions or reports, and that they are free to not answer any question they do not feel comfortable with and to withdraw from the study at any time. All those conducting enumeration of eligible participants and verifying their circumcision status will be male aged 25-39 years; they will be trained on how to approach the participants and how to ascertain the status. The procedure will take place in a private room identified by the respondent.

The blood sample for unlinked testing will be collected by the assistant surgeon while the surgeon is clamping and ligating the bleeding vessels hence the process of sample collection (which will take less than a minute) and will neither interfere with nor delay the process of achieving hemostasis or clumping of the blood vessels.

The sample label will only bear a pre-assigned serial number, date of sample and name of collector.

1. Compensation: Participants in the FGDs will be given actual fare refund of up to a maximum of 200/- and modest compensation for time taken to participate in the discussion, at KSh. 250/-. Since IDIs will take place where the participants are, no fare refund will be given, thus the total compensation for IDI participants will be KShs 250/-. Both at enrollment and endline surveys, participants will be given 250/- as compensation for time. The 250/- for compensation for time is below the minimum wage for a foreman in Kenya; which is Kshs. 324/- per day.
2. Benefits to Participants: All participants enrolled in the study will benefit by obtaining VMMC information contained in the booklet approved by the Ministry of Health (Appendix 17: *All you need to know about VMMC*). In addition, during recruitment, they will have a chance to ask questions and get answers from the RAs, especially those in the IPC and IPC+DSO Locations. They will be informed, during the consenting process that the information obtained from them will help the government of Kenya in getting older men to take up VMMC, an important factor in the fight against HIV acquisition in men and women.
3. Informed Consent: For those coming for VMMC and are 25-39 years, there will be written consent to ask them what influenced their decision to go for the services. Those in DSO and DSO+IPC intervention Locations who go for services in non-DSO sites will be asked why they still prefer these sites despite the availability of DSOs. Apart from the oral consent obtained only during household enumeration, for which we are requesting for waiver of documentation of consent, all consents for the study will be written. Before physical verification of VMMC status can be performed, written consent will be obtained by a male Research Assistant who is fluent in English and Dholuo.

For illiterate persons, an independent witness will be present for the reading of the entire consent and will also sign the consent form. A witness will be a person 18 years old who is literate, is a non-staff, and is accepted by the potential participant to witness the consenting process. Two copies of written consent forms will be signed by the person administering the consent and the participant (and where necessary, a witness); one copy will be stored under lock and key at the research office while another will be given to the participant to carry home for ongoing reference, and to get contact information of study and IRB leadership.

1. Confidentiality/Privacy: As is a requirement of all IRDO staff, all research staff will all undergo ethics training sign confidentiality agreement (Appendix 30: Confidentiality Statement). Research Assistants, VMMC service providers and data staff will be trained to ensure privacy during the data collection and consenting process. Data collection forms will be stored in the field and at IRDO head office in Kisumu, which will be the operating headquarters of the study. No participants will have any identifier on the data forms; names and signatures will only be on the consent forms, which will be kept under lock and key by the Study Coordinator and after signing, will be accessible only to the PIs, Coordinator and IRDO’s Research Officer (EO). Data will be entered in a computer that would be password protected and accessible only to the respective data clerk, the Data Manager, the PIs, the Coordinator and the Research Officer.

Participants will be given contact information of KNH-ERC and CDC IRB on the consent which they can refer to in case they want to report any violation of their rights or if they have any other study-related questions or concerns.

1. Study Staff Training in Handling Human Subjects

Regardless of prior training in research ethics, before protocol implementation, all study staff will undergo a three-day training on ethics and Good Clinical Practices (GCP), with topics covering: what is GCP, importance of GCP, goals of GCP, foundations for ethical conduct in research, the 13 principles of ICH-GCP, responsible persons for GCP compliance, and an overview in ethical issues in handling human subjects. This will be conducted by [name] (PI) in collaboration with officers at the Division of Global HIV/AIDS, CDC Kenya office. Subsequently all staff will be expected to undertake the online [Collaborative Institutional Training Initiative](https://www.citiprogram.org/default.asp) (CITI) pertaining to Human Subjects Research (basic or refresher course for those who have taken the course previously) as well as protocol-based training. The ethics training will be followed by protocol-based training.

1. Sponsor Monitoring: As the study sponsor, the Centers for Disease Control (CDC) may conduct monitoring/auditing of study activities to ensure the scientific integrity of the study and to ensure the rights and protection of study subjects. Monitoring and auditing activities may be conducted by:
   - CDC staff (“internal”)
   - Authorized representatives of CDC (e.g., a contracted party considered to be “external”).
   - Both internal and external parties.

Monitoring or auditing may be performed by means of on-site visits to the Investigator’s facilities or through other communications such as telephone calls or written correspondence. The visits will be scheduled at mutually agreeable times, and the frequency of visits will be at the discretion of CDC. During the visit, any study-related materials may be reviewed and the Investigator along with study staff should be available for discussion of findings.

The study may also be subject to inspection by regulatory authorities (national or foreign) as well as the IECs/IRBs to review compliance and regulatory requirements.

